## Abstract

The postnatal period involves significant emotional and relational shifts that can challenge early mother–infant interactions, particularly under conditions of psychosocial vulnerability (e.g., maternal anxiety/depression) or infant-related risk (e.g., preterm birth). Maternal mentalization, operationalized as Parental Reflective Functioning (PRF), is a key protective factor for sensitive caregiving and dyadic regulation. Objectives: This protocol describes a multicenter, open-label, single-arm feasibility study evaluating a brief, fully online, mentalization-based video-feedback intervention (VFI-RF). The study is designed to assess the feasibility and acceptability of the intervention, rather than its efficacy. We aim to recruit 48 mothers, 24 in each of two risk groups, through socio-health services and neonatal intensive care units. Risk Group 1 will include mothers with clinically significant depressive and/or anxiety symptoms, defined as EPDS > 9 and/or GAD-7 ≥ 10, whereas Risk Group 2 will include mothers of preterm infants, defined as infants born before 37 weeks of gestation. Methods: The intervention consists of 8 + 2 synchronous online sessions over approximately 5 months. Mothers record brief everyday caregiving interactions (~5 min) to review with a trained clinician, focusing on the infant’s internal states and reflective meaning-making. Assessments occur at baseline (T0, infant age ~3 months), post-intervention (T1, ~8 months), and follow-up (T2, ~12 months). Primary feasibility outcomes include recruitment/referral metrics, uptake, retention, assessment completion, missing data, and participant-reported acceptability. Secondary exploratory clinical outcomes include maternal PRF, symptoms, parenting stress, social support, and mother–infant attachment, evaluated via validated self-report questionnaires. Results: The study is designed to evaluate referral and recruitment patterns, intervention uptake, and participant retention, as well as the acceptability and suitability of study procedures and outcome measures for a future controlled trial. Preliminary trajectories of change in maternal reflective functioning and early relational indicators will be examined descriptively and exploratorily. Conclusions: Findings will inform the feasibility and refinement of a brief online mentalization-based video-feedback intervention to support at-risk mother–infant dyads during the first postnatal year. Trial registration: Registered on Open Science Framework, osf.io/6g9ja, date of registration 4th March 2026.

## 1. Introduction

Motherhood experience is accompanied by profound somatic, emotional, and relational changes [1] that contribute to the high degree of psychological complexity of the perinatal period. The transformations associated with this phase are fundamental for shaping the early mother–infant dyadic relationship, particularly with respect to caregiving processes and emerging patterns of mutual regulation. These changes involve individual psychological adjustments in the mother and become highly relevant at the relational level, influencing how she perceives, organizes, and responds to the infant’s signals. In this sense, mentalization, defined as the ability to interpret behavior in terms of underlying feelings, intentions, and thoughts, plays a central role in supporting dyadic exchanges and the stabilization of a secure and growth-promoting relational environment [2]. In parenting, this ability has been operationalized through the construct of Parental Reflective Functioning (PRF), defined as the caregiver’s capacity to identify, reflect upon, and make meaning of mental states within mother–infant interactions [3]. Higher PRF was reported as associated with sensitive caregiving, more coherent interpretations of the infant’s behavior, and favorable socio-emotional outcomes for children [4].

A large body of evidence indicates that maternal vulnerabilities during the perinatal period, such as depressive symptoms, young maternal age, and preterm birth can compromise reflective functioning and the quality of early mother–infant exchanges [5,6]. These difficulties may reduce the mother’s ability to regulate her own emotions and to perceive the infant’s behavior as motivated by specific mental states, increasing the risk of disengaged or intrusive interaction patterns [3]. Such disruptions in early relational processes may contribute to later socio-emotional and attachment difficulties in children, negatively affecting developmental trajectories [7,8].

The present study focuses on two postnatal risk profiles that, although characterized by partially different mechanisms, may converge on relational vulnerability. In mothers with clinically significant anxiety and/or depressive symptoms, risk is primarily related to maternal affective distress. Depressive symptoms may reduce emotional availability, vitality, and sensitivity to infant cues, whereas anxiety may increase threat monitoring, uncertainty, and difficulties in tolerating ambiguous infant signals [7,8]. These processes may interfere with the mother’s capacity to interpret the infant’s behavior in terms of intentional and affective mental states [9,10]. By contrast, in mothers of preterm infants, risk is not necessarily driven by maternal psychopathology alone but may arise from infant-related and contextual factors, including medical vulnerability, early separation, hospitalization, parental fear, and the challenge of reading the cues of an immature or medically fragile infant [11,12].

Despite these differences, both profiles may affect a shared relational pathway: the mother’s capacity to remain emotionally available, observe the infant’s signals, tolerate uncertainty, and construct reflective meanings about the infant’s internal states. Thus, the inclusion of both groups is grounded in the assumption that postnatal relational vulnerability may emerge through different routes, while converging on partially overlapping difficulties in dyadic regulation, cue interpretation, and reflective meaning-making.

In light of the potential impact of postnatal risk conditions on maternal reflective functioning and early mother–infant relationships, preventive and early interventions have increasingly focused on supporting parents’ capacity to recognize, interpret, and respond to their infant’s cues in mental-state terms. Across this field, different intervention approaches have shown promise in enhancing reflective functioning and improving the quality of parent–infant interactions [13,14]. Standard approaches, such as family-centered care, kangaroo mother care, and multisensory developmental interventions, have been associated with improvements in bonding, maternal involvement, and parents’ sense of agency by targeting different components of the dyadic interaction [11,12]. These approaches are clinically valuable, particularly because they can be embedded within neonatal care. However, they often require in-person delivery and substantial institutional resources, and they may not specifically target maternal reflective functioning.

A promising strategy in this field may be video feedback (VF), a technique widely used across several integrated intervention models to support parenting. VF typically involves video-recording brief sequences of mother–infant interaction and reviewing them together with a trained professional, who supports parents in observing the interaction, identifying infant cues, and exploring the dyadic exchange through guided reflection. Systematic evidence has documented consistent improvements in key dimensions of caregiving and interaction quality—including maternal sensitivity, emotional regulation, and dyadic synchrony—as well as beneficial effects on child outcomes, such as attachment security, cognitive and socio-emotional development, and behavioral functioning [15,16,17,18,19]. From a mentalization-based perspective, VF is thought to operate by supporting mothers in recognizing the infant as a psychological agent and fostering their curiosity about the infant’s internal states. This process may in turn promote greater maternal sensitivity, affective attunement, and mentalization capacities [20,21]. It is important to distinguish between the evidence base for VFI and the more specific evidence base for approaching in fully remote, synchronous protocols. Previous evidence concerns VF delivered in face-to-face, home-visiting, clinical, or hybrid formats, or within broader multicomponent parenting interventions [22,23,24]. These studies provide an important rationale for using video-feedback to support parental sensitivity, reflective observation, and dyadic interaction, but they do not directly establish the feasibility or effectiveness of a stand-alone, fully online, synchronous, mentalization-based VFI in postnatal risk contexts. The COVID-19 pandemic further accelerated the transition from in-person to remote delivery of early parenting interventions. In this respect, emerging evidence indicates that telehealth-based VF approaches are both feasible and acceptable for families and may produce outcomes comparable to those achieved through traditional face-to-face formats [25,26].

More recent evidence [27] reinforces the value of stand-alone video-feedback interventions (VFIs) as an effective and flexible approach to supporting early mother–infant relational processes. VFIs are typically brief, cost-effective, and flexible, making them suitable for both preventive and clinical contexts [24,28]. Despite this evidence, several methodological gaps remain. The promising effects of VFIs on parenting and child outcomes are accompanied by inconsistent findings across several domains, including parenting stress and maternal representations [27]. Moreover, although it can be delivered remotely, increasing accessibility and reducing logistical barriers for mothers who are unable to access in-person services, the evidence base for fully remote, synchronous, mentalization-based video-feedback interventions in the postnatal period remains limited [24,27]. Specific challenges of these new approaches need to be examined, including difficulties in ensuring privacy during sessions, reduced clinician control over the therapeutic setting, and the need to establish a sufficiently secure and reflective therapeutic frame through an online medium [29]. Important implementation questions remain unresolved, including whether mothers are willing and able to record and share interaction videos from home, how privacy and confidentiality can be protected, and whether the selected assessment and intervention procedures are acceptable and sustainable for mothers in different postnatal risk conditions.

On this basis, a mentalization-based VFI may be particularly suited to address both shared and profile-specific relational vulnerabilities. The use of a common VFI-RF protocol does not imply that the mechanisms of risk are identical across groups; rather, the intervention targets a shared relational process—parental reflective functioning in everyday mother–infant interactions—while allowing the therapeutic work to be tailored to each dyad’s specific vulnerabilities, strengths, and interactional patterns.

Within this framework, a preliminary single-arm feasibility study represents an appropriate first step to evaluate whether the proposed VFI-RF can be meaningfully and safely implemented in postnatal risk contexts. Before testing its efficacy in a controlled trial, it is necessary to determine whether mothers are willing to engage with a fully online video-feedback format and whether reflective work can be sustained within a remote therapeutic setting. Feasibility evidence is therefore essential to refine the intervention procedures, address potential privacy and implementation barriers, and optimize the design of a future randomized controlled trial [30].

### 1.1. Research Question

This feasibility study aims to determine whether a brief, stand-alone, synchronous online mentalization-based video-feedback intervention (VFI-RF) can be successfully delivered and evaluated among mothers experiencing postnatal risk conditions.

Specifically, the study will address the following research questions:Can eligible mothers be successfully identified, recruited, and retained across the study period?Are the assessment procedures, including questionnaire completion and follow-up assessments, feasible and acceptable to participants?Are the privacy, video-sharing, and data management procedures acceptable and implementable in a fully online format?Do participant-reported satisfaction and qualitative feedback support the acceptability of the VFI-RF intervention and study procedures?

### 1.2. Primary Outcomes

The primary objective of this study will be to generate preliminary evidence on the feasibility and acceptability of delivering and evaluating the VFI-RF intervention for mothers at risk during the postnatal period. In line with the aims of a feasibility study, the primary outcomes focus on feasibility and acceptability indicators rather than intervention effectiveness.

Feasibility will be assessed through enrolment indicators, including the number of mothers referred, the proportion deemed eligible, and the proportion of eligible mothers who provide informed consent. Additional feasibility indicators include intervention uptake, measured as the proportion of VFI-RF sessions attended, retention at baseline and follow-up, reasons for ineligibility or withdrawal, assessment completion, and the extent of missing data on key measures.

Feasibility indicators will be calculated using predefined denominators. Specifically, the number of mothers referred will represent all mothers referred to the study by participating services or who self-refer following study advertisements. Eligibility rate will be calculated as the proportion of referred mothers meeting inclusion criteria. Consent rate will be calculated as the proportion of eligible mothers who provide informed consent. Intervention uptake will be calculated as the proportion of scheduled VFI-RF sessions attended. Retention rates will be calculated as the proportion of consented participants completing each assessment time point (T0, T1, and T2). Assessment completion rates will be calculated as the proportion of participants who complete the planned questionnaires at each assessment wave. All feasibility indicators will be reported for the overall sample and separately for each risk group (i.e., Risk Group 1: anxiety/depression; Risk Group 2: preterm birth).

Acceptability will be assessed using both quantitative indicators and qualitative feedback. The acceptability of the assessment procedures will be evaluated through participants’ views on the number, frequency, duration, content, and mode of delivery of study assessments. Mothers’ experience of the VFI-RF intervention and study procedures will be explored through in-depth feedback on their experiences, satisfaction, and perceived acceptability. Together, these quantitative and qualitative outcomes will be interpreted using pre-specified progression criteria based on a traffic-light system, to determine whether the intervention and study procedures would be suitable for a future larger-scale evaluation.

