#### 2.1.2. Inclusion Criteria

The inclusion criteria for the general eligibility (applies to both groups) will be: (i) mothers in the perinatal/postnatal period aged ≥ 18 years; (ii) adequate knowledge of Italian; (iii) access to a digital device and a stable internet connection sufficient for online sessions and study assessments.

For Risk Group 1 (anxiety/depression), the inclusion criterion will be the presence of clinically significant anxiety and/or depressive symptoms, as identified through screening with the Edinburgh Postnatal Depression Scale (EPDS; cut-off score > 9) and the Generalized Anxiety Disorder 7-item scale (GAD-7; cut-off score ≥ 10). Accordingly, anxiety symptoms alone will qualify mothers for inclusion when the GAD-7 score is ≥ 10, even in the absence of clinically significant depressive symptoms.

For the Risk Group 2 (preterm birth) will be: (i) having given birth to a preterm infant, defined as gestational age < 37 weeks.

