**Figure 2 jcm-15-05271-f002:**
[figure not shown]
Structure and content of the VFI-RF.

**Table 1 jcm-15-05271-t001:** Progression criteria for feasibility and acceptability.

Domain	Area	Indicator	Green	Amber	Red
Feasibility	Enrolment	Mothers referred	≥80% of target	60–79%	<60%
		Eligible among referred	≥60%	40–59%	<40%
		Consented among eligible	≥70%	50–69%	<50%
	Intervention uptake	VFI-RF sessions attended	≥75%	50–74%	<50%
	Retention	Baseline participation	≥90%	75–89%	<75%
		Follow-up participation	≥80%	65–79%	<65%
		Ineligibility/withdrawal reasons across study phases	Infrequent/ non-systematic	Modifiable reasons	Recurrent major issues
	Assessment/data quality	Assessments completed	≥85%	70–84%	<70%
		Missing data on key measures	≤10%	11–20%	>20%
Acceptability	Assessment procedures	Number/frequency acceptable	≥75% positive	50–74%	<50%
		Duration/content/mode acceptable	≥75% positive	50–74%	<50%
	Mothers’ experience	VFI-RF experience	Predominantly positive	Mixed, with modifiable concerns	Predominantly negative or recurrent major concerns
		Satisfaction with VFI-RF/study procedures	≥75% satisfied	50–74%	<50%

**Table 2 jcm-15-05271-t002:** Schedule of participant assessment.

	Pre-Intervention		Post-Intervention	
	Screening	Baseline (T0)	Post-Treatment (T1)	Follow-Up (T2)
Demographics (e.g., age, education, employment and marital status), clinical history, and psychosocial risk variables	✔	✔		
Maternal reflective functioning (PRFQ)		✔	✔	✔
Maternal depression (EPDS)	✔	✔	✔	✔
Maternal anxiety (GAD-7)	✔	✔	✔	✔
Maternal Parenting stress- Short Form (PSI-SF)		✔	✔	✔
Maternal Perceived social support (MSPSS)		✔	✔	✔
Relationship Questionnaire (RQ)		✔		
Maternal postnatal attachment (MPAS)		✔	✔	✔
Child’s emotional and behavioral development (TAPQOL)		✔	✔	✔
Clinical Outcomes in Routine Evaluation- Outcome Measure (CORE-OM)		✔	✔	✔
Satisfaction questionnaire ad hoc			✔	✔

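### The eligibility rate divides by all referred mothers although eligibility is settled only after contact and screening, so losses before screening look like ineligibility and cannot lower the consent rate

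*Protocol article*

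**What the plan says.** Section 1.2 presents the ratios as settled: "Feasibility indicators will be calculated using predefined denominators". The base of the chain is broad: "the number of mothers referred will represent all mothers referred to the study by participating services or who self-refer following study advertisements". The next two steps are "Eligibility rate will be calculated as the proportion of referred mothers meeting inclusion criteria" and "Consent rate will be calculated as the proportion of eligible mothers who provide informed consent". Table 1 attaches bands to both. The row "Eligible among referred" is green from 60%, amber from 40% to 59% and red below 40%. The consent row is green from 70%, amber from 50% to 69% and red below 50%.

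Other sections show steps between referral and eligibility. Under section 2.1.5, service staff only judge who might qualify, the research team then makes contact, and agreeing to be contacted is expressly not agreeing to take part. Under section 2.1.2, Risk Group 1 status is established "as identified through screening with the Edinburgh Postnatal Depression Scale" and the GAD-7. Table 2 has its own Screening column, which holds both scales together with demographics and clinical history. Section 2.1.6 sends the baseline link to mothers who meet the criteria and have consented.

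**The concern.** The recruitment pathway has a contact step and a screening step, but the indicators pass straight from referred to eligible and have no category for eligibility not assessed. Applied exactly as written, the rule counts a referred mother who was never reached or never screened in the same way as one who was screened and failed a criterion. She is also absent from the consent rate, which describes only mothers who had already accepted screening.

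The two rows call for different responses. A low eligibility rate points to the criteria or to referral targeting. A low consent rate points to unwillingness to join the study. The introduction names willingness to engage with a fully online format as something to be settled before a controlled trial, and the first research question in section 1.1 asks whether eligible mothers can be identified and recruited. Under these ratios, unwillingness shown before screening cannot lower the indicator meant to detect it.

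**Working it through.** The plan gives no figure to reproduce. The check is arithmetic on the stated ratios.

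**Inputs from the article.** The two ratios (section 1.2) and the bands 60/40 and 70/50 (Table 1).

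**Inputs not in the article (assumed).** *u*, the share of referred mothers not screened; *e*, the eligible share among those screened; *c*, consent among those found eligible.

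**Step 1. Formulas.**
- Eligibility rate as defined = (1 − *u*) × *e*
- Eligibility rate among screened = *e*
- Consent rate as defined = *c*, whatever *u* is
- Consented/referred = (1 − *u*) × *e* × *c*

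**Step 2. Loss at which the eligibility row changes colour.** It leaves green when (1 − *u*)*e* < 0.60, that is *u* > 1 − 0.60/*e*. It turns red when *u* > 1 − 0.40/*e*.

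| *e* among screened | leaves green at *u* | turns red at *u* |
|---|---|---|
| 60% | any loss | above 33.3% |
| 70% | above 14.3% | above 42.9% |
| 80% | above 25% | above 50% |
| 90% | above 33.3% | above 55.6% |

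**Step 3. Worked example (assumed *u* = 30%, *e* = 80%, *c* = 75%).** Of 100 referred, 70 are screened, 56 are eligible and 42 consent.
- As defined: eligibility 56/100 = 56% (amber); consent 42/56 = 75% (green).
- With a screened stage: screened/referred 70/100 = 70%; eligible/screened 56/70 = 80% (green); consent 42/56 = 75% (green).
- Consented/referred: 42/100 = 42% under either scheme.

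Here the amber eligibility result comes entirely from the 30 unscreened mothers, and Table 1 has no row that separates them out.

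**Step 4. How far the consent rate could be affected.** If all 30 were refusals with the same 80% eligible share (24 mothers), consent would be 42/(56 + 24) = 52.5% (amber). If all 30 were eligible refusers, it would be 42/(100 − 14) = 48.8% (red), where 14 = 70 − 56 is the number confirmed ineligible. These are bounding cases. Without counts of not reached and declined, the data cannot place the trial between 48.8% and 75%.

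**The case against.** Several points on the other side have force.

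- Eligible among referred is an openly labelled yield, useful for planning referral volume in a later trial. That stands as a reason to keep a referral-based yield, but not as the only measure of eligibility.
- The overall yield is the same under either scheme. This is true. The defect lies in how the loss is divided between rows.
- Table 1 has a row for reasons for ineligibility or withdrawal, and section 2.2.1 reads all indicators together with qualitative feedback. Some of the loss may become visible this way, so no single colour dictates the decision. Neither provision changes a ratio or its colour, though, and a mother never screened is neither documented as ineligible nor withdrawn.
- The pathway is narrower than it may look. Staff hand over information first and interested mothers are then contacted, so some refusals occur before a mother counts as referred. This limits the likely size but does not remove the loss after referral.

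A reader might also infer that the two risk groups are scored differently, because the Group 2 criterion, "having given birth to a preterm infant, defined as gestational age < 37 weeks", is known at birth while Group 1 status needs questionnaires. The documents do not support this. Language, device and internet requirements and the exclusions apply to both groups, and several need contact with the mother. Table 2 does not restrict screening to Group 1. Group 1 is recruited partly through mental-health services, where symptom status may already be known. No difference between the groups in how refusals are counted can be shown.

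**Conclusion.** The point holds. The article fixes denominators that omit a step in its own recruitment pathway, so loss before screening lowers the eligibility rate and leaves the consent rate untouched. The direction follows from the ratios alone and needs no assumption.

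The size does depend on assumptions, since the article gives no figure for loss before screening, eligibility among screened mothers, or consent. If 80% of screened mothers are eligible, the eligibility row turns amber once loss exceeds 25%; the corresponding figures are 14.3% at 70% eligible and 33.3% at 90%. Smaller losses change no colour.

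A reader might go further and infer that the reported consent rate will be overstated by a known amount. It cannot be quantified: some unscreened mothers will simply not have been reached, and others would have failed a criterion. The overall yield is unaffected. The change is worth making before recruitment starts, because losses that are not logged by type may not be recoverable later.

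**What to change.** In section 1.2 and Table 1:

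1. Add a screened stage, defined as completion of the Table 2 Screening column, between referred and eligible.
2. Report screened/referred as its own row, with separate counts for mothers not reached and mothers who declined before screening. State whether the row carries bands or is descriptive.
3. Define the eligibility rate as eligible/screened, and confirm before recruitment that the 60/40 bands are meant for that denominator.
4. Keep consented/eligible, and add consented/referred as overall yield.
5. Apply the same rules in both risk groups.

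Consented/(referred minus confirmed ineligible) may be shown, but only as a lower bound on acceptance, because it treats every unassessed mother as an eligible refuser.

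The cost is two extra fields in the recruitment log, one extra row in Table 1, and recruitment figures that may look less favourable. According to section 2.1.5, recruitment had not begun when the article was written, so no data would need to be reclassified if the change is made before it starts.
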